## Study Objectives

The primary objective of this study is to assess the feasibility of delivering a multimodal surgical prehabilitation service to surgical oncology patients. The secondary objectives are to explore the effectiveness of the program using clinical, physical, and patient-reported outcome measures. The specific research questions guiding this study design are listed in **Box 1**.

**BOX 1**. Study Research Questions.Feasibility Research Questions:RQ1a: How many referrals for prehabilitation will be received and what are the identified indications for prehabilitation?RQ1b: Does a surgeon’s bedside assessment of frailty (as indicated by referral and reason for referral) correspond with established frailty indices?RQ1c: What percentage of referred patients participate in prehabilitation?RQ1d: What are the demographic and medical characteristics of patients who are referred to for prehabilitation?RQ1e: What factors contribute to participants choosing either FBP or HBP?RQ1f: What is the ‘prehabilitation window’ for participants (i.e., time from treatment decision to surgery)?RQ1g: What is the adherence rate to the multimodal components defined by the prehabilitation protocols?RQ1h: Is prehabilitation safe within a clinical model of care (i.e., number and nature of adverse events)?RQ1i: What are the barriers and facilitators to prehabilitation?RQ1j: What are the various costs and potential cost savings associated prehabilitation?Exploratory Effectiveness Research Questions:RQ2a: What changes in clinically relevant outcomes do participants experience by the week prior to surgery and up to 90 days after surgery?RQ2b: Compared to usual care, what effect does prehabilitation have on peri- and postoperative outcomes (up to 90 days after surgery)?(RQ, Research Question)

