## Methods

### Design

This is a pragmatic, preference-based, non-blinded, non-randomized trial to assess the feasibility and estimates of effectiveness of a clinically integrated, multimodal prehabilitation program for frail surgical oncology patients in an urban academic health center in Toronto, Ontario, Canada. Participant flow throughout the study is presented in **Figure 1**. The initial study protocol and subsequent amendments related to the COVID-19 pandemic have been approved by the University Health Network research ethics board.

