### Sample Size

A period of trial enrolment, rather than target sample size, was selected to inform expected rates of referral for a clinical service. The trial anticipates receiving 150 referrals for prehabilitation over 12 months. We estimate that one third of all referred patients will decline the intervention but will consent to making their hospital records related to their pending cancer surgery available for research (hereafter referred to as ‘usual care’ participants).

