### Study Outcomes

Participant data to assess feasibility and derive estimates of effect are collected from the participants’ referrals, at the baseline assessment, within 1 week prior to surgery, and at 30 and 90 days postoperatively.

The total number of referrals and the rate at which they are received (per month) will be reported. To characterize the patients referred to the program, the following are collected from all referral forms (including usual care participants and those who decline research): referring surgical service; reason for referral; frailty level (*via* the Clinical Frailty Scale (3), embedded into the referral); cancer type; indicated surgery; referring healthcare practitioner type (*i.e.* physician, surgeon, clinic nurse, *etc.*), and participant demographics (age, sex, and general geographic location). The enrolment rate will be calculated as [# of enrolled participants]/[# of referred participants]. The frequency and reasons for declining participation in the study, declining prehabilitation (*i.e.*, usual care participants), and drop-out will be reported and compared using descriptive statistics of demographic and referral data.

Given the importance of scheduling and timing for prehabilitation relative to the date of surgery, several relevant time periods will be reported. The time from program referral to the date of surgery will be reported and is referred to as the ‘prehabilitation window’. We will also report the total preoperative period (time between consent for surgery and date of surgery) and prehabilitation duration (time from baseline assessment to surgery).

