### Analytic Plan

The analytic plan is described for prehabilitation implementation feasibility outcomes and exploratory analyses of prehabilitation effects. In line with comparative effectiveness research, presentation of confidence intervals will be emphasized for the purpose of accurately reflecting the actual data as well as directly addressing the uncertainty of the data. All quantitative analyses will be conducted in R (R Foundation for Statistical Computing, Vienna, Austria) and an alpha of.05 will be used.

Demographic and disease characteristics of all referred patients, as well as prehabilitation and usual care participants**’** will be summarized with appropriate parametric and non-parametric statistics. Reasons for ineligibility, declined participation in the study or intervention, as well as reasons for choosing FBP or HBP will be tallied. Group comparisons for referral information (surgical service, type of cancer, type of surgery, age, sex, and geographic location) will be assessed by one-way analysis of variance (ANOVA) for continuous and Chi-square test for categorical variables and described across FBP, HBP, usual care, and participants who decline participation. Baseline demographic and disease-related variables will be compared between study participants (FBP, HBP and usual care) ***via*** one-way ANOVA for continuous variables and Chi-square test for categorical variables.

Adherence to the interventions will be summarized dichotomously as meeting or not meeting the prescribed intervention components across each domain (exercise, nutrition, psychology, and smoking cessation). Reasons for deviations will be thematically categorized and summarized by frequency and percentage. Retention rates will be calculated as a total percentage of dropouts at the presurgical time point to the total participants enrolled for FBP and HBP. Reasons for dropout will be summarized using frequencies and percentage for each prehabilitation arm. Reported safety or adverse events will be summarized using frequencies and percentage for each group.

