To provide an estimate of effect of HBP and FBP, point estimates and 95% confidence intervals will be calculated for changes in physical fitness, patient-reported outcomes from baseline to the 90-day time point using linear mixed effect models. Estimated mean hospital length of stay for HBP, FBP, and usual care, as well as between-group differences, will also be conducted using a linear mixed effect model. Incidence rate ratios and estimating rate differences for postoperative complication, readmission, and morbidity for prehabilitation in reference to usual care at 30 and 90 days after surgery will be made using Poisson regression. Tukey HSD will be used to adjust for multiple comparisons. In the presence of outliers, bootstrapping regression coefficient methodology will be done to obtain valid confidence intervals.

Semi-structured interviews regarding participant satisfaction as well as facilitators and barriers with the intervention will be transcribed verbatim and undergo qualitative content analysis. Initial transcript sample readings will be independently done by two researchers. Preliminary themes will be noted, and differences will be resolved, and duplications will be eliminated. Themes and content will be analyzed descriptively. Coding, linking, and retrieving the qualitative data will be conducted using NVivo software (QSR International, Melbourne, AUS).

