There are several strengths of this study. First, the pragmatic, preference-based trial design with robust implementation feasibility outcomes and measures of effectiveness will add important information to the prehabilitation literature that is currently lacking in these areas. Second, the prehabilitation interventions are multimodal and comprehensive within each modality intended to replicate gold-standard practice. Moreover, the interventionists represent the appropriate scopes of practice and clinical professions most qualified and likely to be involved in an interprofessional, multimodal clinical prehabilitation service. Third, by including a usual care arm, we have a control comparator for effect size estimates. Fourth, we have amended our research protocol to respond to the evolving context of the COVID-19 pandemic by pivoting towards contactless study participation. This study also has noteworthy limitations. The sample size will likely lack the statistical power to draw precise conclusions about the effect of the interventions. Similarly, in the absence of an RCT design, our interpretations of comparisons with usual care participants may be limited due to group differences in those who do versus those who do not wish to engage in prehabilitation. Interpretation of the findings will also be limited to the types of surgeries for which prehabilitation precedes which may be skewed to the physicians and healthcare teams who are in favour of prehabilitation and refer patients to our study. This highlights potential sampling and participation biases as participants will more likely be referred and participate in our program if their healthcare team implicitly endorses it by virtue of discussing it and making a referral. Similarly, the breadth of cancer surgeries and their extreme heterogeneity within a relatively small sample will limit sub-group analyses related to estimates of intervention effect.

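### The Analytic Plan names no control for confounding in the self-selected prehabilitation versus usual-care comparison, so its estimates may mix case mix with effect

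*Protocol article*

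**What the plan says.** Under Design, the article states: "This is a pragmatic, preference-based, non-blinded, non-randomized trial". Under Sample Size, the usual-care group is made up of referred patients who turn down the intervention but release their hospital records. They are expected to be one third of about 150 referrals. No sample size is set for any comparison: "A period of trial enrolment, rather than target sample size, was selected to inform expected rates of referral for a clinical service".

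Study Objectives gives the comparison exploratory standing ("The secondary objectives are to explore the effectiveness of the program"), but research question RQ2b in Box 1 is worded causally: "Compared to usual care, what effect does prehabilitation have on peri- and postoperative outcomes".

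The Analytic Plan handles group differences in two unconnected steps.

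- **Description.** ANOVA and chi-square tests are run across groups. The first set is introduced as "Group comparisons for referral information (surgical service, type of cancer, type of surgery, age, sex, and geographic location". A second set covers baseline demographic and disease variables.
- **Outcome models.** Length of stay is compared across home-based, facility-based and usual-care groups with a linear mixed model. Rate ratios and differences for complications, readmission and morbidity "for prehabilitation in reference to usual care at 30 and 90 days after surgery will be made using Poisson regression". Tukey HSD (for multiplicity) and bootstrapping (for outliers) are named. Covariates, weights, matching and strata are not.

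Study Outcomes lists what every referral form supplies, usual care included: service, reason for referral, frailty level (via "the Clinical Frailty Scale (3), embedded into the referral"), cancer type, planned surgery, referrer type, age, sex and location. The same section bases the hospital cost impact on a unit bed-day cost applied to the differences between those who enrolled in prehabilitation and those who did not.

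The Discussion concedes that "our interpretations of comparisons with usual care participants may be limited due to group differences". It also counts the usual-care arm among the study's strengths, as a control for effect sizes.

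**The concern.** Patients choose their own group, and the reasons for declining prehabilitation (frailty, distance, a short wait, a minor operation) can also bear on complications and length of stay. The eligible operations run from breast lumpectomy to lung resection, and the Discussion itself calls the surgical mix extremely heterogeneous. If the groups differ in that mix, a crude rate ratio can show benefit or harm where there is none. The same distortion would pass into the bed-day cost difference.

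Testing for baseline differences does not remove them. Nothing in the Analytic Plan carries the test results into the outcome models. The list of referral variables to be compared also leaves out frailty level and reason for referral, although the Introduction treats frailty as a leading driver of surgical risk.

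**Working it through.** The article gives no power, effect size or expected ratio for RQ2b, so there is no stated figure to reproduce. The checks below show what an uncontrolled contrast could do.

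**Group sizes (Sample Size).** Usual care: 150 × 1/3 = 50. Prehabilitation: at most 150 − 50 = 100, fewer if some patients decline research altogether.

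**Illustration 1: surgical mix, no true effect.** Let *a* and *b* be the shares of major surgery in prehabilitation and usual care. The complication rate for major surgery is 50%, the Introduction's 30-day figure for major abdominal cancer surgery. The 10% for minor surgery and all the splits are assumptions.

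Crude ratio = [0.5*a* + 0.1(1 − *a*)] / [0.5*b* + 0.1(1 − *b*)]

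| *a* (prehabilitation) | *b* (usual care) | Rates | Crude ratio |
|---|---|---|---|
| 0.40 | 0.60 | 0.26 / 0.34 | 0.76 |
| 0.45 | 0.55 | 0.28 / 0.32 | 0.88 |
| 0.55 | 0.45 | 0.32 / 0.28 | 1.14 |
| 0.60 | 0.40 | 0.34 / 0.26 | 1.31 |

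**Illustration 2: a milder binary risk factor, no true effect.** Let the factor multiply risk by RR, with prevalence *p*₁ in prehabilitation and *p*₀ in usual care (all assumed).

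Crude ratio = [1 + *p*₁(RR − 1)] / [1 + *p*₀(RR − 1)]

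- RR 1.5, 40% vs 60%: 1.2 / 1.3 = 0.92
- RR 2.0, 40% vs 60%: 1.4 / 1.6 = 0.88
- RR 2.0, 30% vs 60%: 1.3 / 1.6 = 0.81
- RR 2.0, 60% vs 40%: 1.6 / 1.4 = 1.14
- Equal prevalence: 1.00

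The bias can go either way, and it vanishes when the factor is balanced.

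**Are the planned baseline tests a safeguard?** With 100 vs 50 patients and two-sided alpha 0.05, power to detect an imbalance of 40% vs 60% is about 64%. For 40% vs 50% it is about 21%. A non-significant test is therefore weak evidence that the groups are comparable.

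**Precision for comparison.** Assume 50% complications in both groups of 100 and 50. The 95% interval for the ratio extends by these factors either side:

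- Poisson variance: exp(1.96 × √(1/50 + 1/25)) = 1.62
- Robust variance: exp(1.96 × √(0.5/50 + 0.5/25)) = 1.40

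**The case against.** The strongest reply is that the article is silent rather than wrong. It names model families and lists no model terms. It nowhere calls the models crude or univariable, and covariate lists often sit in an analysis plan that is not shown here. A reader might infer that the models contain only a group term. The text does not say so, and that reading is not supported.

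Silence still counts here. The Analytic Plan goes down to the software, the multiplicity method and the handling of outliers. In a self-selected comparison, confounder control decides what the contrast means, so it is more than a detail. The Discussion treats group differences only as a limit on interpretation and mentions no analytic remedy.

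Four further points have weight:

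- The comparison is exploratory and the selection problem is disclosed. This lowers the severity. It does not make a crude contrast answer a question about effect.
- Usual-care patients come from the same referral stream and meet the same eligibility criteria, including a stated indication for prehabilitation. This restriction removes part of the confounding, but not differences in surgery, age or degree of frailty within that stream.
- Frailty is not dropped from description altogether. Study Outcomes plans a descriptive comparison of demographic and referral data across those who decline the study, decline prehabilitation or drop out. The gap is confined to the list in the Analytic Plan.
- Even a spurious ratio of 0.76 would lie inside an interval that spans a factor of 1.40 to 1.62. Wide intervals do limit the claims that can be made. They express sampling error only, though, and a biased contrast centres them in the wrong place.

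**Conclusion.** The point holds in a limited form. The Analytic Plan names no confounder control for a self-selected comparison that RQ2b words as an effect and that also drives the hospital cost impact. Followed as written, it may mix case mix with intervention effect.

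A reader might go further and conclude that RQ2b will report case mix as an effect. The documents do not support that. They give no distribution of any risk factor by group, so neither the size nor the direction of bias can be derived. The range of 0.76 to 1.31 rests on an assumed 10% rate for minor surgery, on assumed splits, and on a 50% rate quoted for major abdominal surgery rather than for this mixed population. The milder assumptions give 0.81 to 1.14.

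This should be fixed, but it is not critical: the primary objective is feasibility, and no primary result depends on this comparison.

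**What to change.** 1. Prespecify an adjusted prehabilitation versus usual-care contrast, by overlap weighting or a small regression model. Use variables already on the referral form for all groups: Clinical Frailty Scale, age, sex, and surgery or service grouped by risk. Enrolment period is not a listed form item; if it is used, take it from the referral date.
2. Report the adjusted estimate beside the crude one for complications, readmission, morbidity and length of stay, and carry both into the hospital cost impact.
3. Add Clinical Frailty Scale and reason for referral to the group comparison in the Analytic Plan, and report standardised differences.
4. Describe the RQ2b results as associations, and state that confounding by motivation and health behaviour remains after adjustment.

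**Cost.** The changes are to analysis wording and need no new data collection. Some precision is lost. With about 50 usual-care participants and a very mixed set of operations, the covariate set must stay small or the model may become unstable. The covariates should be fixed before outcomes are analysed, so that they are not chosen with results in view.

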### Protocol Adaptations in Response to the COVID-19 Pandemic

COVID-19 containment measures have reduced elective surgery volumes around the world. Reduced surgical capacity has led to longer wait times for elective procedures and patients are experiencing declining physiological and psychosocial health in the unsettling context of social distancing, community service closures, and economic hardship. This loss in health is likely to be most profound for older patients and those with complex medical needs. Consequently, the extended waiting time is likely to negatively impact disease progression and surgical tolerance that may lead to higher rates of adverse surgical outcomes, ultimately compounding COVID-19-related health system strain. Given that prehabilitation may play an important role in mitigating the deterioration of health and well-being during extended surgical wait times, this study implemented several amendments to accommodate pandemic-related restrictions and barriers to healthcare in an attempt to maintain the opportunity for prehabilitation participation for planned but unscheduled, or delayed, cancer surgery. A summary of the amendments approved by the institutional ethics board is provided in **Box 2**.

**BOX 2**. COVID-19 Pandemic-Related Study Accommodations.1. Extension of enrolment period by at least 6 months to accommodate pauses in research and to initiate contactless study protocols2. Accept form-fillable PDF referrals by email from clinicians (*versus* referrals by fax)3. Informed consent is obtained verbally, by phone, with informed consent documentation emailed to participants to be completed and returned at their next hospital visit (*e.g.*, date of surgery, post-operative clinic visit)4. All interactions between participants and study staff, including the baseline assessment, are completed by telephone or web conferencing (Microsoft Teams, Redmond, Washington, USA)5. Exercise equipment, manuals, and protein supplementation are mailed to participants6. All exercise sessions are intended to be conducted at-home and employ the same exercise parameters for HBP described in **Table 1**. Additional emphasis on strategies to maintain social distancing is provided for those who are engaging in outdoor exercise.7. Study outcomes requiring an in-person assessment (*e.g.*, 6MWT, body composition, grip strength) are omitted during in-person research restrictions, and only data derived from questionnaires and the electronic medical record are collected for exploratory analyses of effectiveness

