**Methods:**

This is a pilot pragmatic clinical trial conducted in a large academic hospital in Toronto, Ontario, Canada to assess feasibility of clinical implementation and derive estimates of effectiveness. Feasibility data include program referral rates, enrolment and attrition, intervention adherence and safety, participant satisfaction, and barriers and facilitators to programming. The study aims to receive 150 eligible referrals for adult, English-speaking, preoperative oncology patients with an identified indication for prehabilitation (*e.g*., frailty, deconditioning, malnutrition, psychological distress). Study participants undergo a baseline assessment and shared-decision making regarding the intervention setting: either facility-based prehabilitation or home-based prehabilitation. In both scenarios, participants receive an individualized exercise prescription, stress-reduction psychological support, nutrition counseling, and protein supplementation, and if appropriate, smoking cessation program referrals. Secondary objectives include estimating intervention effects at the week prior to surgery and 30 and 90 days postoperatively. Outcomes include surgical complications, postoperative length of stay, mortality, hospital readmissions, physical fitness, psychological well-being, and quality of life. Data from participants who decline the intervention but consent for research-related access to health records will serve as comparators. The COVID-19 pandemic required the introduction of a ‘virtual program’ using only telephone or internet-based communication for screening, assessments, or intervention was introduced.

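### The pandemic amendment removes the facility stream, but the stated analysis keeps FBP, HBP and usual care with no virtual category or period factor, so FBP contrasts and uptake shares can be confounded with period.

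*Protocol article*

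**What the plan says.** The Prehabilitation Program section builds the design on a choice: each participant settles on FBP or HBP in a shared decision-making conversation at baseline, and trends in that preference are a stated interest. RQ1e in Box 1 asks what drives the choice.

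Box 2 (Protocol Adaptations in Response to the COVID-19 Pandemic) changes delivery:
- Contact: "All interactions between participants and study staff, including the baseline assessment, are completed by telephone or web conferencing".
- Exercise: "All exercise sessions are intended to be conducted at-home and employ the same exercise parameters for HBP".
- Enrolment: "Extension of enrolment period by at least 6 months to accommodate pauses in research and to initiate contactless study protocols".
- In-person outcomes "are omitted during in-person research restrictions, and only data derived from questionnaires and the electronic medical record are collected".

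The abstract gives the new mode its own name, a virtual program, "using only telephone or internet-based communication for screening, assessments, or intervention was introduced".

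The analysis sections still describe the two-stream design. Under the Analytic Plan, "reasons for choosing FBP or HBP will be tallied", and baseline variables and length of stay are compared across FBP, HBP and usual care. Complications and readmissions are modelled for prehabilitation against usual care. Under Study Outcomes, the cost-effectiveness ratio (ICER) is FBP minus HBP, and for referrals "the rate at which they are received (per month) will be reported". No virtual group, period factor or treatment of paused months appears in any of these places.

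**The concern.** While restrictions last, nobody can be an FBP participant. FBP is then drawn only from in-person periods. Usual care is drawn from both periods, because Box 2 keeps referral and consent running remotely. Virtual participants have no named group. If they are counted as HBP, that arm also spans both periods.

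Comparing FBP with a group that spans both periods mixes delivery setting with pandemic-era surgical access. The article expects that period to matter: the adaptations section and the Discussion both predict that longer waits will bring more complications, poorer recovery and higher cost. The limitations in the Discussion cover self-selection and heterogeneity of surgery, but not period.

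Two feasibility results are also exposed, and feasibility is the primary objective. FBP/HBP uptake would count people who were offered only one setting. The monthly referral rate, which the Sample Size section gives as the reason for fixing an enrolment period, has no stated denominator once enrolment is extended to cover pauses.

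**Working it through.** The article gives no power calculation, effect size or SD, so there is no derived figure to reproduce. Its one planning figure is 150 referrals in 12 months, or 150/12 = 12.5 per month.

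**1. Which groups can exist when (Prehabilitation Program; Box 2, items 2–4 and 6).**

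| Group | In-person period | Restriction period |
|---|---|---|
| FBP | yes | no |
| HBP by choice | yes | no, since no alternative is offered |
| Virtual | no | yes |
| Usual care | yes | yes |

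Virtual delivery also differs from the HBP first described. The Exercise section has every participant shown the exercises at the facility before starting; Box 2 makes all contact remote.

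**2. Uptake share if virtual participants are pooled into HBP.** Let v be the virtual share of prehabilitation participants and q the share preferring FBP when both are offered. The article gives neither, so both are assumed. Apparent HBP share = v + (1 − v)(1 − q).
- q = 0.5, v = 1/3: 0.333 + 0.667 × 0.5 = 0.667.
- q = 0.5, v = 1/2: 0.5 + 0.5 × 0.5 = 0.75.
- Range at v = 1/2: 0.85 for q = 0.3 (true HBP share 0.70) and 0.65 for q = 0.7 (true share 0.30).

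Restricting to people offered both settings returns 1 − q.

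**3. FBP versus HBP under pooling.** Virtual share of the pooled HBP arm: w = v/[v + (1 − v)(1 − q)]. FBP contains none. If the restriction period shifts an outcome by d, HBP minus FBP is biased by w × d. With q = 0.5:

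| v | w | bias, d = 0.2 SD | bias, d = 0.5 SD |
|---|---|---|---|
| 0.25 | 0.40 | 0.08 SD | 0.20 SD |
| 0.50 | 0.67 | 0.13 SD | 0.33 SD |
| 0.75 | 0.86 | 0.17 SD | 0.43 SD |

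For d = 0.5 SD, with q from 0.3 to 0.7 and v from 0.25 to 0.75, the bias runs from 0.16 to 0.45 SD. The values of d are illustrative; the article predicts a direction but no size.

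**4. FBP versus usual care on length of stay, however virtual participants are coded.** If a share u of usual care comes from the restriction period, usual care minus FBP is biased by u × d. For u = 1/2 and d = 0.5 SD this is 0.25 SD.

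**5. Pooled prehabilitation versus usual care (complications, readmissions).** The bias is (v − u) × d. It is zero at v = u = 0.5, and ±0.2 × d at v = 0.5 with u = 0.3 or 0.7. Period confounds here only if uptake changed between periods.

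**6. Referral rate, as a separate scenario.** Suppose the extension is the minimum six months and all six are a full pause. Then 150 referrals over 18 calendar months give 150/18 = 8.3 per month, against 150/12 = 12.5 over open months. With 12.5 per open month and a three-month pause, the calendar rate would be 12.5 × 15/18 = 10.4.

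**The case against.** The strongest reply is that the article never says virtual participants will be counted as HBP. Box 2 borrows only HBP's exercise parameters, and the abstract names a separate program. This stands: a reader might infer that pooling is the plan, but the text leaves the class undefined. Steps 2 and 3 are therefore conditional on pooling. Step 4 is not.

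A second reply is that Box 2 summarises amendments within a condensed article, and that period terms and denominators belong in an analysis plan. In part this stands: it cannot be shown that the full analysis was left unamended. But the article itself fixes the comparison groups and the ICER formula, and describes an amendment under which one of those groups cannot occur. That is a conflict between stated passages, not omitted detail.

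Other strong readings are tempting but unsupported:
- That every outcome contrast is affected alike. Complications and readmissions are compared only for prehabilitation as a whole against usual care, which is step 5, not step 3. Walk test, grip strength and body composition are not collected during restrictions, so they are lost rather than mixed.
- That the tally of reasons is corrupted. Someone given no choice has no reason to record; the exposure is in the uptake shares.
- That the 67% and 8.3 figures describe one course of events. The same six months cannot be both virtual enrolment and a full pause, and a month-by-month referral report would show a pause anyway.
- That the results blend two different trials. HBP was already home exercise with telephone support, and the home-only phase may be temporary. Two delivery and surgical-access periods is the accurate description.

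**Conclusion.** The point holds in limited form and should be fixed before analysis. Run as written, FBP versus usual care on length of stay carries calendar period whenever some usual-care participants enrol under restrictions. FBP versus HBP (length of stay, questionnaire changes, adherence by stream, ICER) carries it if virtual participants are placed in HBP, and uptake shares would then count people without a choice.

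The sizes depend on the assumed preference, virtual share and period shift. The direction of the uptake error does not: pooling can only raise the apparent HBP share. The referral figure depends on whether paused months are counted, which the article leaves open.

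This does not undermine the study. The effectiveness contrasts are declared exploratory, the feasibility results are descriptive, and all of them can be separated by period afterwards. Setting the rule now avoids choosing the coding after the results are seen.

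**What to change.** Amend the analysis wording as follows:
1. Report virtual participants as a separate stream wherever FBP and HBP are shown.
2. Limit RQ1e, uptake shares, FBP–HBP contrasts and the ICER to participants enrolled while both options were open.
3. Include an in-person/virtual period term in the length-of-stay model and in the pooled prehabilitation-versus-usual-care models, noting that in the latter it matters only if uptake changed between periods.
4. Report monthly referrals by period, over months open to referral, with paused months identified.

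No change to delivery or data collection is needed; enrolment date and delivery mode should already be on record. The cost is precision. FBP–HBP contrasts lose any virtual participants who would have been pooled, so their intervals widen somewhat. FBP versus usual care will rest mainly on usual-care participants from the in-person period.
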